## Abstract

**Background/Objectives:** Children with Autism Spectrum Disorder (ASD) often display heightened sensitivity to simple auditory stimuli, but have difficulty discriminating and integrating multiple phonological features (segmental: consonants and vowels; suprasegmental: lexical tones) at the syllable level, which negatively impacts their communication. This study aims to investigate the neural basis of segmental, suprasegmental and combinatorial speech processing challenges in Mandarin-speaking children with ASD compared with typically developing (TD) peers. **Methods:** Thirty children with ASD and thirty TD peers will complete a multi-feature oddball paradigm to elicit auditory ERP during passive listening. Stimuli include syllables with single (e.g., vowel only), dual (e.g., vowel + tone), and triple (consonant + vowel + tone) phonological deviations. Neural responses will be analyzed using temporal principal component analysis (t-PCA) to isolate overlapping ERP components (early/late MMN), and representational similarity analysis (RSA) to assess group differences in neural representational structure across feature conditions. **Expected Outcomes:** We adopt a dual-framework approach to hypothesis generation. First, from a theory-driven perspective, we integrate three complementary models, Enhanced Perceptual Functioning (EPF), Weak Central Coherence (WCC), and the Neural Complexity Hypothesis (NCH), to account for auditory processing in ASD. Specifically, we hypothesize that ASD children will show enhanced or intact neural discriminatory responses to isolated segmental deviations (e.g., vowel), but attenuated or delayed responses to suprasegmental (e.g., tone) and multi-feature deviants, with the most severe disruptions occurring in complex, multi-feature conditions. Second, from an empirically grounded, data-driven perspective, we derive our central hypothesis directly from the mismatch negativity (MMN) literature, which suggests reduced MMN amplitudes (with the exception of vowel deviants) and prolonged latencies accompanied by a diminished left-hemisphere advantage across all speech feature types in ASD, with the most pronounced effects in complex, multi-feature conditions. **Significance:** By testing alternative hypotheses and predictions, this exploratory study will clarify the extent to which speech processing differences in ASD reflect cognitive biases (local vs. global, per EPF/WCC/NCH) versus speech-specific neurophysiological disruptions. Findings will advance our understanding of the sensory and integrative mechanisms underlying communication difficulties in ASD, particularly in tonal language contexts, and may inform the development of linguistically tailored interventions.

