#### 1.1.1. Lexical Tone Processing

In tonal languages like Mandarin, pitch contours, which are conveyed through F0 variations at the syllable level, create lexical contrasts (e.g., “妈” [mā] with a flat tone means “mother,” while “骂” [mà] with a falling tone means “scold”). In contrast, non-tonal languages (e.g., English) use pitch for prosodic functions like intonation and emphasis [13,14,15]. This distinction is critical for understanding auditory processing in ASD, where research reveals a dissociation between non-speech and speech-related pitch processing. While individuals with ASD often exhibit intact or enhanced sensitivity to simple, non-speech pitch changes (e.g., demonstrating faster reaction times and stronger MMN responses to frequency deviants [16]), they struggle to integrate pitch information into more complex contexts [17,18]. For instance, despite heightened pitch discrimination, individuals with ASD struggle with auditory stream segregation [19], suggesting a bias toward local pitch features at the expense of integrating these features into different voice streams.

This pattern is particularly evident in tonal language studies. Children with ASD show reduced MMN amplitudes in response to Mandarin and Cantonese tone contrasts, even though they exhibit enhanced MMN responses to non-speech pitch deviations [20,21]. They also do not show the typical enhancement of MMN for between-category tone contrasts compared to within-category acoustic differences, indicating difficulties with categorical perception of lexical tones [22]. These findings suggest that while basic pitch detection may be preserved or heightened in ASD, the integration of dynamic F0 contours with phonological and linguistic context is problematic [20,23,24,25]. Thus, the core challenge lies not in detecting pitch changes, but in assigning them linguistic meaning within a speech signal.

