### 1.4. The Current Study

A key innovation of this study is the fine-grained analysis of auditory mismatch responses across varying levels of speech feature complexity. Unlike previous research, which has largely focused on isolated speech elements such as pitch, vowels, or consonants, and thus neglected their dynamic interplay, we aim to investigate how segmental (e.g., consonants, vowels) and suprasegmental (e.g., tone) features are processed and integrated in Mandarin-speaking children with ASD.

We employ a multi-feature oddball paradigm to examine whether children with ASD differ from typically developing (TD) peers in their sensitivity to single-, dual-, and triple-feature speech deviations. Neural responses will be assessed via the mismatch negativity (MMN), focusing on differences in amplitude, latency, and temporal coordination across processing stages. Although the P3a component is sometimes analyzed in the literature, its inconsistent reporting means it will not be a primary focus of our exploratory study.

Our study addresses four key questions:Do children with ASD show diminished MMN responses to speech feature deviations, with greater impairment for complex, multi-feature contrasts?Do ERP differences reflect processing delays that cascade across time, rather than isolated amplitude reductions?How do concurrent changes in tone, consonant, and vowel interact in ERP responses, and do children with ASD show atypical integration patterns in MMN?Given tone’s lexical role in Mandarin, do children with ASD show the most pronounced differences in tone-related conditions, suggesting a language-specific signature of speech processing difficulty?

To address these questions, we adopt a dual-framework approach that distinguishes between theory-driven and data-driven hypotheses. Our theoretical framework integrates three complementary models, WCC, EPF, and NCH, to explain auditory processing in ASD. Together, these models suggest a dissociation as our central hypothesis with specific prediction outlined in Table 1: enhanced or intact MMN responses to single-feature deviants (e.g., consonant or vowel changes), but attenuated or delayed responses to multi-feature deviants (e.g., C + V, V + T, C + V + T), reflecting impaired integration under increasing cognitive load. In this framework, consonants and vowels are tentatively classified as local, segmental features, while tone and multi-feature combinations are treated as global, integrative features.

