#### 2.2.2. Oddball Paradigm and Experimental Procedure

The experiment adopts a multi-feature oddball paradigm with /ba1/ as the standard stimulus, which appears in 50% of the trials (980 instances). The remaining 50% of the trials (980 instances) consist of seven types of deviant stimuli, each comprising 7.14% of the total. The deviant types include single-feature changes (e.g., from /ba1/ to /ba4/, a change in flat tone to falling tone) and combined-feature changes (e.g., from /da1/ to /bu4/, which has consonant + vowel + tone changes). The full set of stimuli is summarized in Table 3 below:

Stimulus presentation is controlled using the E-Prime 2.0 software. Auditory stimuli are delivered binaurally via a Presonus Firebox audio interface and KOSS PORTA PRO headphones, with the sound intensity calibrated to 65 dB SPL. Each stimulus has a duration of 300 ms, and the stimuli are presented with a randomized stimulus onset asynchrony (SOA) ranging from 950 to 1050 ms, corresponding to an interstimulus interval (ISI) of 650 to 750 ms. The entire experimental session lasts approximately 35 min. To allow participants to adapt to the auditory environment, 20 standard stimuli are presented prior to data collection; these are be excluded from the formal analysis. Participants are instructed to passively listen to the stimuli while watching a self-chosen silent animation throughout the experiment to maintain visual engagement and minimize movement artifacts (see Figure 1a,b).

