#### 3.1.1. t-PCA-Level Predictions (P)

P1 (Component Variance): The proportion of variance explained by temporally decomposed MMN components (eMMN, lMMN) will be lower in the ASD group for multi-feature deviants (V + T, C + T, C + V + T), reflecting less structured neural responses under high integrative demand.

P2 (Factor Scores): Factor scores for MMN-related components will be significantly reduced in the ASD group, particularly for tone-involving conditions (T, V + T, C + T, C + V + T), consistent with a global integration deficit.

P3 (Temporal Dynamics): The ASD group will show a delayed peak in late MMN (lMMN) components across all conditions, with the greatest delay observed for triple-feature deviants, supporting NCH’s prediction of cascading processing delays.

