**Figure 3 brainsci-15-00905-f003:**
[figure not shown]
Workflow of RSA applied to ERP data from a multi-feature oddball paradigm.

**Table 1 brainsci-15-00905-t001:** Tentative Predictions for the Seven Stimulus Conditions (Based on EPF/WCC/NCH) Condition.

	Processing Type	Prediction in ASD	EPF + NCH Account	WCC + NCH Account
Consonant only	Local	↑ or = MMN amplitude ↓ or = MMN latency	Enhanced perception of phonetic detail	Intact
Vowel only	Local	↑ or = MMN amplitude ↓ or = MMN latency	Enhanced formant processing	Intact
Tone only	Global	↓ MMN amplitude ↑ MMN latency	Reduced prosodic integration	Impaired due to global integration load
C + V	Mixed/Global	↓ MMN amplitude ↑ MMN latency	Disruption due to multiple feature load	Integration weakness
V + T	Global	↓↓ MMN amplitude ↑↑ MMN latency	Disrupted holistic processing	Poor feature binding
C + T	Global	↓↓ MMN amplitude ↑↑ MMN latency	Disrupted holistic processing	Failure to form unified percept
C + V + T	Global	↓↓↓ MMN amplitude ↑↑↑ MMN latency	Collapsed integration under complexity	Strongest integration failure

Note: ↑ represents significant increase. ↓ represents significant decrease. = represents similar results when comparing MMN responses in ASD group with those in the TD group. Double/Triple arrows indicate magnitude increment/decrement.

**Table 2 brainsci-15-00905-t002:** Specific Predictions Based on MMN Literature-Based Predictions for Each Stimulus Condition.

Condition	MMN Amplitude in ASD	Latency in ASD	Reduced Left-Hemispheric MMN Dominance
Consonant only	↓	↑	Predicted—based on broader speech processing literature
Vowel only	= or ↓	↑	Predicted—but may be less pronounced than for consonants
Tone only	↓	= or ↑	Predicted—particularly for lexical tones
C + V	↓↓	↑↑	Predicted—likely pronounced
V + T	↓↓	↑↑	Predicted—key for tonal languages
C + T	↓↓	↑↑	Predicted—reflects integration challenge
C + V + T	↓↓↓	↑↑↑	Predicted—most pronounced reduction expected

Note: ↑ represents significant increase. ↓ represents significant decrease. = represents similar results when comparing MMN responses in ASD group with those in the TD group. Double/Triple arrows indicate magnitude increment/decrement.

**Table 3 brainsci-15-00905-t003:** Phonological Stimuli: Standard vs. Deviant Feature Variations.

Stimulus Type	Stimulus	Feature(s) Changed
Standard	/ba1/	None
Deviant 1	/ba4/	Tone change
Deviant 2	/bu1/	Vowel change
Deviant 3	/da1/	Consonant change
Deviant 4	/bu4/	Tone + Vowel Change

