Deviant 5	/da4/	Tone + Consonant Change
Deviant 6	/du1/	Vowel + Consonant Change
Deviant 7	/du4/	Tone + Vowel + Consonant Change

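### Question 4 would read larger group differences in tone conditions as language-specific, but the design has no non-speech or non-tonal comparison, and an unmatched tone comparison also carries feature count

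*Protocol article*

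**What the plan says.** Section 1.4 lists four key questions. The fourth, introduced by the lexical role of tone in Mandarin, asks: "do children with ASD show the most pronounced differences in tone-related conditions, suggesting a language-specific signature of speech processing difficulty". The Abstract's significance statement says the study will help separate cognitive biases from another source of speech processing differences: "versus speech-specific neurophysiological disruptions".

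The tone-involving set appears in prediction P2 (section 3.1.1): "particularly for tone-involving conditions (T, V + T, C + T, C + V + T), consistent with a global integration deficit". Table 3 defines the deviants from the standard /ba1/. For example, /bu4/ is "Tone + Vowel Change" and /da4/ is "Tone + Consonant Change". Section 2.2.2 says the deviant trials "consist of seven types of deviant stimuli, each comprising 7.14% of the total".

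Section 2.2.1 describes all eight stimuli as Mandarin monosyllables, and section 2.1.2 requires every participant to be a native Mandarin speaker. Section 1.4 also expects the group differences in amplitude and latency to grow from single to dual to triple deviants.

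On the background evidence, section 1.1.1 reports that children with ASD have reduced MMN to lexical tones "even though they exhibit enhanced MMN responses to non-speech pitch deviations".

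**The concern.** Two separate things stand between the data and the reading that question 4 proposes.

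**Missing comparison.** To call a deficit specific to speech, one has to show that it is absent or smaller for a comparable non-speech sound. To call it specific to a tonal language, one needs speakers of a non-tonal language. The article uses the first standard when it reviews earlier work: section 1.1.1 sets lexical tone against non-speech pitch, and section 1.1.3 infers a speech-specific attention problem from an effect seen for vowels and not for non-speech deviants. The study has neither comparison.

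**Overlap with complexity.** Three of the four tone-related deviants change more than one feature, and the only triple deviant contains tone. If group differences grow with the number of changed features, as the article itself expects, tone-related conditions can look worst without tone contributing anything.

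One of the four key questions could therefore receive a positive answer, worded as language-specific, from data that fit a general pitch effect or a general complexity effect equally well.

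**Working it through.** **1. Weights.** Section 2.2.2 gives 980 deviant trials of 1,960 in total and seven types. 980/7 = 140 trials per type, and 140/1,960 = 7.14%, which reproduces the stated share. Conditions can therefore be weighted equally.

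**2. Features changed (Table 3).**
- Tone-related: T 1, V+T 2, C+T 2, C+V+T 3. Mean (1+2+2+3)/4 = 2.00.
- Others: C 1, V 1, C+V 2. Mean (1+1+2)/3 = 1.33.

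By symmetry, the vowel-involving and consonant-involving sets also average 2.00 against 1.33 for their complements.

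**3. What an unmatched comparison would show.** Write the group difference in a condition as a + k × (features changed) + t × (tone changed). Then:
- tone-related mean minus the rest = t + k(2.00 − 1.33) = t + 0.67k;
- T minus mean(C, V) = t + k(1 − 1) = t;
- mean(V+T, C+T) minus C+V = t + k(2 − 2) = t.

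With t = 0, the unmatched comparison still gives 0.67k and the matched ones give 0. The value of k is not known from the document.

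**4. The article's own amplitude predictions,** counting arrows of reduction as ranks, not as effect sizes.
- Table 2: tone-related mean 2.00; the rest 1.00 to 1.33, because vowel is given as equal or reduced. At equal feature count the tone excess is 0 to 0.5 for single deviants and 2 − 2 = 0 for dual deviants. These predictions would produce the question 4 pattern almost wholly through feature count.
- Table 1, counting an equal or enhanced response as no reduction: a tone excess of at least 1 arrow for single deviants and 2 − 1 = 1 for dual deviants. The table attributes it to global integration, not to language specificity.

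**5. Can tone and count be separated?** Yes. Over the seven deviants, a model with intercept, count and tone has full rank (3). The correlation of count with tone is 0.47, so VIF = 1/(1 − 0.47²) ≈ 1.29.

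**6. Can speech be separated from pitch?** No. Non-speech stimuli: 0 of 8. Non-tonal-language groups: none. Even a tone excess t at equal feature count could be a response to F0 contour in general. Section 2.2.1 adds that spectral tilt and formant trajectories are not quantified, so equal salience across the three features is not shown either.

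**7. Readings side by side.** Much the same result, with the largest effects where tone is involved, is read as language-specific in section 1.4 and as a global integration deficit under P2. In section 5, where the largest effects are in multi-feature and tone-involving contrasts, it is read as a general processing burden. Nothing in the design decides between the first reading and the other two.

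**The case against.** The strongest reply is that no section plans to pool the tone-related deviants against the rest. Question 4 asks where differences are largest and names no test, and an article may leave the exact contrast to a fuller plan. Tables 1 and 2 predict condition by condition, so the comparisons at equal feature count are already visible there. The RSA in section 2.3.4 includes a Base Feature-Count model alongside the tone-, vowel- and consonant-weighted ones. If tone-related is meant relative to vowel-related or consonant-related, the sets are balanced on count. All of this stands. A reader might infer that the article has fixed a confounded analysis, or that tone is uniquely confounded; the document supports neither.

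Two further inferences also go too far. One is that the Abstract's dichotomy would be decided by the tone comparison: section 5 judges the competing accounts on the whole pattern across conditions. The other is that P2 repeats the problem: it speaks of global integration and draws no language-specific conclusion.

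It can also be said that question 4 only suggests, that its wording may mean tied to a tonal language rather than to speech, and that the study is exploratory. The hedging lowers the strength of the claim but does not supply a comparison. The tonal-language reading fails as well, for lack of a non-tonal group. Section 6 acknowledges isolated syllables, passive listening, sample size and heterogeneity, but not this gap. An analysis plan could settle the feature-count part; it cannot create a non-speech condition.

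**Conclusion.** The point holds in two parts of different strength.

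- **Firm:** the design cannot support a language-specific reading of a tone excess. This rests only on the stated stimulus set and eligibility criteria, and no analysis of these data can repair it.
- **Conditional:** if tone-related deviants are compared with the remaining ones without regard to feature count, a pure count deficit of k per feature yields a spurious tone excess of 0.67k. This assumes equal weights and a deficit linear in count. The article does not commit to that comparison, and its stimuli allow it to be avoided.

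Question 4 remains answerable as a question about tone within Mandarin speech. The correction is worth making before results are interpreted, because it changes what a positive answer may be said to show.

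**What to change.** 1. State the test for question 4 as a group × tone effect with feature count held constant. Either use the two matched contrasts, T versus mean(C, V) and mean(V+T, C+T) versus C+V, or fit a group × tone term adjusted for group × feature count on all seven deviants.
2. In section 1.4, replace the language-specific signature with a tone-related difference within Mandarin speech. Soften the speech-specific wording in the Abstract. P2 needs no change.
3. Add to section 6 that there is no non-speech pitch condition and no non-tonal-language group, so a tone effect cannot be told apart from a general F0 effect.

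The cost is one pre-stated contrast or model on data already being collected, plus short text changes. The claim becomes narrower. In the matched version C+V+T drops out, because it has no tone-free counterpart. The adjusted model keeps it but assumes that the count effect is linear.

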## 2. Materials and Methods

### 2.1. Participants

#### 2.1.1. Sample Size Justification and Ethics

The sample size for this study was determined using G*Power (version 3.1) [67]. A priori power analysis was conducted using an MANOVA: Repeated measures, within-between interaction framework as the study compares two groups (ASD vs. TD) with multiple MMN measures. Assuming a relatively large effect size (Cohen’s f = 0.25), the analysis indicated that a total sample size of at least 52 participants (approximately 26 per group) would be required to achieve a power of 0.80 at a significance level of α = 0.05.

This study will be conducted in accordance with the ethical guidelines and approved by the Human Research Ethics Committee for Non-Clinical Faculties at South China Normal University. Written informed consent is obtained from the legal guardians of all participating minors, and assent is secured from the children themselves. Participants are recruited voluntarily through collaboration with the Guangzhou Kangna School and Guangzhou Yongxing School, with explicit inclusion/exclusion criteria to ensure suitability. Risks are considered minimal, as the EEG procedure poses no physical or psychological harm, and participants are free to withdraw at any time without penalty. All EEG and behavioral data collected will be stored securely on institutional servers equipped with firewalls and advanced security protocols compliant with relevant data protection regulations. Hard copies will be securely locked and accessible only to designated research personnel. Data will be anonymized with unique identifiers to protect participant confidentiality. Analysis datasets will be fully de-identified. Secure long-term storage and data sharing practices will adhere strictly to institutional ethics guidelines and the oversight of the Ethics Committee of the School of Psychology, South China Normal University, which reviewed and approved the study protocol.

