**Figure 2 brainsci-15-00905-f002:**
[figure not shown]
t-PCA pipeline for ERP data in the multi-feature oddball paradigm. (**A**) Data Matrix Setup. The matrix is labeled by Conditions × Time Points × Electrodes, representing trials collected across different stimulus types. (**B**) Covariance Matrix. Covariance matrix is essentially a mathematical tool that helps capture how the data varies over time and across different participants and conditions. (**C**) Principal component analysis. After we obtain the covariance matrix, the next step for t-PCA is to perform eigenvalue decomposition of the covariance matrix to extract the Principal Components from it. These principal components can be seen as new variables extracted from the original EEG signal, which reflect the change pattern of the maximum variance in the data. (**D**) Rotation. The principal components are adjusted using rotation techniques, such as Promax rotation, to improve interpretation. The purpose of the rotation is to make the interpretation between the individual principal components clearer and allow them to have correlations that are more in line with the actual electrical activity of the brain. (**E**) Component identification. By rotating the components, we can begin to identify the individual ERP components that make sense, such as eMMN, lMMN, and P3a. (**F**) Back-Projection and Reconstructed ERP. Components being projected back to ERP space. We multiply the loading matrix of each principal component with the factor scores under each condition to obtain the reconstructed waveform. The reconstructed waveforms contain the specific variation structure of each principal component in the ERP signal, and these waveforms can be interpreted in µV units, like traditional ERP waveforms. (**G**) Amplitude Extraction and Statistical Comparison. This final panel shows mean amplitude extraction from the reconstructed ERP data and reflects statistical testing (e.g., *t*-tests, ANOVA) to assess group differences or condition effects.

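### The 52 participants given for 80% power at f = 0.25 do not follow from the test named in section 2.1.1, which needs at least 128

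*Protocol article*

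**What the plan says.** Section 2.1.1 names G*Power 3.1 and states: "A priori power analysis was conducted using an MANOVA: Repeated measures, within-between interaction framework". The reason given is that "the study compares two groups (ASD vs. TD) with multiple MMN measures". The effect size is introduced as "Assuming a relatively large effect size (Cohen’s f = 0.25", and the result, at α = 0.05, is that "a total sample size of at least 52 participants (approximately 26 per group) would be required to achieve a power of 0.80". The number of measurements entered is not given.

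Section 2.1.2 plans 30 children with ASD and 30 TD children, 60 in total. Section 2.2.2 says that the non-standard trials "consist of seven types of deviant stimuli, each comprising 7.14% of the total".

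**The concern.** The central hypotheses concern the group-by-condition pattern. Section 1.4 and Table 1 predict intact or enhanced responses to isolated consonant or vowel changes and weaker responses to multi-feature deviants. Table 2 predicts deficits that grow with the number of features. The within-between interaction is the natural test of such patterns, and section 2.1.1 names it.

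For that test, f = 0.25 with 26 per group looks far too favourable. With only two measurements, the interaction reduces to a two-group comparison of a difference score with d = 2f = 0.5, and 26 per group is well short of what d = 0.5 needs. Further measurements raise the numerator degrees of freedom and hence the required N. The label attached to 0.25 also disagrees with the usual convention (0.25 medium, 0.40 large).

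This is the study's only sample-size justification. A reader who accepts the 80% may give a non-significant interaction more weight than the named test supports.

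**Working it through.** **Inputs.** From 2.1.1: k = 2 groups, f = 0.25, α = 0.05, power 0.80, stated N = 52. From 2.1.2: planned N = 60. From 2.2.2: seven deviant types, so m = 7 is the natural number of measurements. Because m is not stated, the check runs from m = 2 upwards.

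**Formula.** With two groups the multivariate interaction has s = min(k − 1, m − 1) = 1, and

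- df1 = m − 1
- df2 = N − m
- λ = N·f²
- power = P[F′(df1, df2, λ) > F(0.95; df1, df2)], where F′ is noncentral F.

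Taking f directly as the multivariate effect size, neither a correlation nor a sphericity term enters, so m is the only unknown.

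**Attempt to reproduce 52.** At N = 52 and f = 0.25, λ = 52 × 0.0625 = 3.25.

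- m = 2: F′(1, 50), critical value 4.03, power 0.42.
- m = 7: F′(6, 45), critical value 2.31, power 0.20.

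Neither approaches 0.80.

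**Required N at f = 0.25 for 80% power**

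| m | N (λ = N·f²) | N (λ = df2·f²) |
|---|---|---|
| 2 | 128 | 130 |
| 3 | 158 | 161 |
| 4 | 179 | 183 |
| 7 | 225 | 232 |
| 8 | 237 | 245 |

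The last column uses the other common noncentrality convention (Muller-Peterson). N rises with m throughout, so the minimum is 128, and 128/52 ≈ 2.5. As a cross-check at m = 2, the normal approximation for two means with d = 0.5 gives 126.

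**At the planned 60.** λ = 60 × 0.0625 = 3.75. Power is 0.48 at m = 2 and 0.23 at m = 7. The smallest f with 80% power is about 0.37 at m = 2 and 0.51 at m = 7.

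**Where 52 could have come from**

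- f = 0.40 with m = 2: N = 52, power 0.807. At f = 0.40 the requirement is 64 for m = 3, 73 for m = 4 and 92 for m = 7, so this account works only for two measurements.
- 0.25 entered as f² (f = 0.5): 53 at m = 5 with λ = N·f², or 52 at m = 4 with λ = df2·f².
- A between-groups repeated-measures test at f = 0.25, m = 8, correlation 0.3: N = 52.
- A univariate interaction at f = 0.25, m = 3, correlation 0: N = 54.

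None of these matches what 2.1.1 describes.

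**The case against.** The strongest reply is that the study may never use the multivariate test. The Figure 2 legend says of the amplitude analysis that "This final panel shows mean amplitude extraction from the reconstructed ERP data and reflects statistical testing", with t-tests and ANOVA as examples. For a univariate repeated-measures interaction in which f is scaled by the correlation, f = 0.25 with m = 7 and correlation 0.5 needs only 18 participants; with m = 7 and correlation 0 it needs 34. On that footing 60 is ample. This stands as a limit on the conclusion: f does not mean the same thing in the two procedures, and low power of every possible planned analysis is not shown. It does not rescue 2.1.1, which names the multivariate procedure and gives no correlation.

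Second, section 6 concedes that sample size may limit power for interaction effects and calls the findings preliminary, and the study describes itself as exploratory. That softens the consequence. It neither withdraws nor quantifies the 80% in 2.1.1.

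Two stronger readings are tempting. A reader might infer that 0.25 is simply a slip for 0.40, since the label would then fit and 52 results. But that needs m = 2, which the article does not state, and the f² account fits about as well. A reader might also infer that the investigators will treat a null interaction as proof of intact processing. The protocol does not say so.

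**Conclusion.** The stated sample size is wrong for the test named. At f = 0.25, α = 0.05 and 80% power, the two-group MANOVA within-between interaction needs at least 128 participants, and 225 with the seven deviants, against 52 stated and 60 planned. Under that test, power at f = 0.25 runs from 0.42 (m = 2) down to 0.20 (m = 7) with 52, and from 0.48 down to 0.23 with 60. Calling 0.25 relatively large is a separate, smaller error.

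The conclusion rests on f being the effect size of the named multivariate test and on m being 2 or more. The choice between the two noncentrality conventions moves the required N by a few participants only. What is established is that procedure, f and N do not belong together. Which of them is at fault cannot be settled from the document.

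**What to change.** In section 2.1.1:

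- name the procedure that matches the planned group-by-condition test;
- state the number of measurements, the effect-size definition and any assumed correlation;
- reconcile f with N, and drop the description of 0.25 as relatively large;
- report power or the detectable effect at the planned 60.

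If the MANOVA interaction over seven deviants is kept, the text could read: with 30 children per group, the test has 80% power for f of about 0.51 and about 23% power at f = 0.25.

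The cost is wording only, with no extra participants and no change to the design. If the named test is kept, the stated power becomes less favourable.
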